### Inclusion and exclusion criteria

2.2

Inclusion criteria for enrollment are described as follows: males or females aged 25 to 65 years old, with no limitation of range of shoulder motion; those who can be diagnosed as SIS by excluding fracture, dislocation, degenerative arthropathy, os acromiale, subacromial spur, and calcific tendinitis in plain radiography; those with shoulder pain lasting more than 2 months from the onset, the pain is worse when sleeping sideways or lifting the arm over the head, with positive on the Neer or Hawkins test, with more than 50 mm on pain of visual analogue scale (VAS); those who are able to communicate sufficiently with the researcher and complete a questionnaire with minimal help; those who have pledged not to receive treatment other than the prescribed treatment within the period of study; those who agree with written informed consent voluntarily.

Exclusion criteria are described as follows: those who have trauma history of shoulder surgery, fracture, dislocation; those with disorders of the cervical spine or upper extremity that have a significant impact on the shoulder; those who have received injection treatment on the shoulder within the past 6 months; patients with fracture, dislocation, degenerative arthropathy of the glenohumeral joint or acromioclavicular joint, os acromiale, subacromial spur and calcific tendinitis of the shoulder in plain radiography; those with positive findings in a physical examination (drop arm test, empty can test) for exclusion of rotator cuff tear; those with positive findings in the Yergason test for exclusion of biceps tendinitis; those who have been diagnosed with a frozen shoulder (adhesive capsulitis) in a range of motion test; those with pacemaker insertion or significant arrhythmia on electrocardiography); pregnant or breastfeeding females with positive findings in the urine pregnancy test before random assignment, or those who are unable or unwilling to use contraceptive methods (hormonal contraceptives, condoms, intrauterine devices, etc.) to avoid pregnancy throughout the entire study period; those with mental disorders who cannot follow the study protocol; those who were considered as unsuitable for participation by the researcher.

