#### Primary outcome

2.5.1

The primary outcome will be the change 100 mm pain VAS for shoulder pain. For rating severity of shoulder pain intensity, 100 mm pain VAS will be assessed by the subjects self-checking and evaluating the degree of pain using the 100 mm line, which is described at one end as “no pain” and at the other end as “worst pain imaginable.” This outcome will be measured at visits 2, 3, and 4. At each measurement, the shoulder pain intensity that occurs during the Neer Test and the Hawkins Test will be measured.^[11]^

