### Sample size

2.6

For calculating the sample size, we searched for a clinically significant difference of VAS in previous studies. There was no previous study with the same experimental and control groups as ours evaluating the efficacy with the VAS as a primary outcome. So referring to the previous clinical trial, which included a broad population of patients with various musculoskeletal conditions, we determined a significant difference of VAS as 2 point.^[12–14]^ From the study comparing fluoroscopically guided and blind corticosteroid injections, standard deviation was conservatively assumed to be 2.3.^[15]^ We calculated the sample size with 80% power at a significance level of 0.05. The sample size is 42 in total and 21 for each group. Assuming a dropout of about 20%, about 54 patients in total (27 per each group) may be needed.

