### Statistical analysis

2.7

For statistical analysis, a full analysis set (FAS), per-protocol set (PPS), and the safety set will be used. Both the FAS analysis and the PPS analysis will be used for the efficacy evaluation. PPS will be the main set according to the principle of intentionality treatment.

Evaluation of the primary outcome will be conducted by VAS change after 2 treatment sessions (visit 3) compared with baseline (visit 2). To compare 2 groups, 2-sample *t* test will be used. The paired *t* test will be used for analysis in each group. For the interaction of treatment over time, repeated measures analysis of variance will be used. And secondary outcomes (modified CMS and SPADI) are evaluated by the same methods as the primary outcome. The Neer test and Hawkins test will be summarized as frequency and percentage, and the comparison between the 2 groups will be performed using the *χ*^2^ test or the Fisher exact test. The accuracy ratio acupuncture is calculated by comparing the ratio between the 2 groups.

For safety evaluation, a 2-sample *t* test or Mann–Whitney *U* test will be conducted in case of continuous variable, and *χ*^2^ test or Fisher exact test will be conducted for assessing the differences of incidence of adverse events.

In the case of missing data, the method of last observation carried forward (LOCF) will be performed.

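### The primary t test on VAS change makes no use of visit 2 VAS as a covariate; ANCOVA would be modestly to clearly more precise at almost no cost

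*Protocol article*

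**What the plan says.** All references are to the protocol article.

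- Section 2.7 (Statistical analysis) defines the primary variable: "Evaluation of the primary outcome will be conducted by VAS change after 2 treatment sessions (visit 3) compared with baseline (visit 2".
- The same section names the between-group test: "To compare 2 groups, 2-sample *t* test will be used". No covariate is mentioned.
- It carries the method over to two secondary scales: "secondary outcomes (modified CMS and SPADI) are evaluated by the same methods as the primary outcome".
- The only other between-group model for VAS is "For the interaction of treatment over time, repeated measures analysis of variance will be used". It does not name baseline as a covariate.
- Section 2.5.1 (Primary outcome) shows that the baseline is available: "This outcome will be measured at visits 2, 3, and 4". Section 2.5.2 gives the same visits for the secondary outcomes.
- Section 2.2 sets an entry threshold: "with more than 50 mm on pain of visual analogue scale (VAS".
- Section 2.6 (Sample size) states "we determined a significant difference of VAS as 2 point" and "standard deviation was conservatively assumed to be 2.3", without saying whether that is the SD of a single score or of a change.
- Section 2.3 describes 1:1 randomisation and mentions no stratification on baseline pain.

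**The concern.** Subtracting the baseline amounts to assuming that each extra unit of pain at visit 2 predicts exactly one extra unit at follow-up. Pain scores usually regress towards the mean, so the true slope is below 1, and two things follow.

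1. The change score carries baseline noise that a fitted slope would remove, so the treatment difference is estimated less precisely than the data allow.
2. If the arms differ at visit 2 by chance, subtracting the whole difference over-corrects. The estimate is unbiased over all randomisations, but it is shifted given the baselines actually observed.

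With 21 evaluable patients per group, chance differences at baseline are not negligible. The remedy uses a value already measured at visit 2.

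**Working it through.** **Inputs.** From Section 2.6: difference 2 points, SD 2.3, power 80%, alpha 0.05, 21 per group, about 20% dropout. I read 2 points as 20 mm on the 100 mm scale and take the test as two-sided. The baseline-to-follow-up correlation r is not in the article; I assume 0.3 to 0.7.

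**Step 1: the plan's own figure.** n per group = 2 × (1.960 + 0.842)² × (2.3/2)² = 20.8, so 21 (42 in total). With dropout, 21/0.8 = 26.25, so 27 per group (54 in total). Both stated figures reproduce. Exact power of the t test (noncentral t) at 21 per group is 78.5%.

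**Step 2: validity.** Simulating the change-score t test at 21 per group with no treatment effect gives a type I error of 5.0% to 5.1% for r = 0.3, 0.5 and 0.7.

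**Step 3: equal SD s at both visits.** The variance of change is 2(1 − r)s². The ANCOVA residual variance is (1 − r²)s². Their ratio is (1 + r)/2.

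| r | Variance ratio | Saving | ANCOVA SD if 2.3 is the SD of change | Power at 21 per group (t test: 78.5%) |
|---|---|---|---|---|
| 0.3 | 0.65 | 35% | 1.85 | 92.6% |
| 0.5 | 0.75 | 25% | 1.99 | 88.7% |
| 0.7 | 0.85 | 15% | 2.12 | 84.6% |

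These powers use 39 rather than 40 residual degrees of freedom. Allowing also for chance imbalance in the covariate costs about 1 percentage point or less.

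**Step 4: the entry threshold.** Under a linear model with slope b, Var(change) = residual variance + (1 − b)² × Var(baseline). Selecting on the baseline leaves b and the residual variance alone and shrinks Var(baseline). The change score therefore becomes less noisy and moves towards ANCOVA.

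Assume an unselected SD of 23 mm at both visits, so that b equals the unselected r, an unselected mean of 60 mm, and visit 2 VAS confined to 50 to 100 mm. The truncated normal variance is then 0.312 × 23², a baseline SD of 12.9 mm.

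| Unselected r | Var(change)/23² | ANCOVA/23² | Saving |
|---|---|---|---|
| 0.3 | 0.91 + 0.49 × 0.312 = 1.063 | 0.91 | 14% |
| 0.5 | 0.75 + 0.25 × 0.312 = 0.828 | 0.75 | 9% |
| 0.7 | 0.51 + 0.09 × 0.312 = 0.538 | 0.51 | 5% |

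Unselected means of 50 or 70 mm also give about 5% to 15%. Ignoring the upper end of the scale, with mean 60 mm, gives 20%, 14% and 8%. At r = 0.5 the SD of change falls from 23.0 mm to about 21 mm.

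If 2.3 is the SD of change in such a truncated sample, savings of 5%, 10% and 15% correspond to ANCOVA powers of 80.5%, 82.5% and 84.6% against 78.5%.

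**Step 5: chance imbalance.** If 2.3 is the SD of a single score, the SE of the baseline difference is 2.3 × √(2/21) = 0.71 points. A one-SE imbalance shifts the change-score estimate by (1 − r) × 0.71 = 0.50, 0.35 or 0.21 points at r = 0.3, 0.5 or 0.7, against a target of 2. With the truncated SD of 12.9 mm, the SE is 12.9 × √(2/21) = 4.0 mm (0.40 points) and the shifts are 0.28, 0.20 and 0.12 points.

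**The case against.** The strongest reply is that nothing is broken. Randomisation protects the type I error, the sample size matches the test named, and a change score does use the baseline. The statistical analysis plan is not shown and could add an adjusted analysis. All of that stands, and it makes this a matter of efficiency rather than validity. It does not remove the point, because the article itself fixes the unadjusted comparison as the primary one.

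It is also fair that the gain depends on quantities the article does not give. With k = baseline SD / follow-up SD, the variance ratio is (1 − r²)/(1 + k² − 2rk). At r = 0.5 this is 0.75 for k = 1, 0.89 for k = 0.8 and 1.00 for k = 0.5. A 25% saving is therefore the equal-SD case, not a general result.

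Three stronger readings are tempting, and the document does not support them.

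- **That the 50 mm entry threshold makes the change score noisier.** It lowers r, but it also shrinks the baseline variance, and the net effect is the opposite (Step 4).
- **That the planned test has only about 64% power, against 82% for ANCOVA.** This needs 2.3 to be the SD of a single score, r = 0.3 and equal SDs at both visits. On the same reading with r = 0.7, the t test has 94.4%. Nothing in the article selects the unfavourable case.
- **That the Neer and Hawkins comparison should be limited to patients positive on that test at visit 2.** Entry requires only one of the two tests to be positive, so some patients may start negative on the other. The article does not say how many, and the restriction would discard patients from a small trial. That trade-off is debatable.

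**Conclusion.** The point holds as a worthwhile improvement, not as an error that invalidates the analysis. The planned t test is valid and its sample size reproduces. ANCOVA would cut the variance of the treatment difference by 15% to 35% if the SDs are equal at both visits, and by about 5% to 15% if the entry threshold fully truncates visit 2 VAS. The truth may lie between. Section 2.1 has a 1-week run-in, and Section 2.5.1 measures the outcome during the Neer and Hawkins tests, so the score used for entry may not be the visit 2 score.

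These ranges rest on an assumed r of 0.3 to 0.7, a linear relation between baseline and follow-up and, for the truncated case, an assumed unselected SD of 23 mm. Under that linear model the ANCOVA residual variance never exceeds the variance of the change score. Apart from the small cost of estimating the slope, the change is therefore a gain or neutral.

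**What to change.** Amend Section 2.7 as follows.

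- Make the primary analysis an ANCOVA of VAS at the primary time point on treatment group, with visit 2 VAS as covariate. Report the adjusted difference with its 95% confidence interval.
- Name the visit. Section 2.7 describes visit 3 as following both sessions, whereas Section 2.1 places the second session at visit 3. These passages must be reconciled before the time point is fixed.
- State that outcome and covariate are the same measurement, since Section 2.5.1 records pain during both the Neer and the Hawkins test.
- Use the same model for modified CMS and SPADI, each with its own visit 2 value.
- Keep the two-sample t test on change as a supportive analysis.
- Fix all of this before unblinding.

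The cost is one degree of freedom and a protocol amendment, which has to go through the ethics committee and the registration. No new data and no larger sample are needed.

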#### Secondary outcomes

2.5.2

The secondary outcomes will be the tests for impingement sign and function of the shoulder joint. These will be measured at visits 2, 3, and 4. To assess improvement of impingement syndrome, we will perform the Neer test and Hawkins test.^[11]^ Function of the shoulder joint will be assessed by the Modified Constant Murley Score scale (Modified CMS) and the Shoulder Pain And Disability Index (SPADI). We will also evaluate the patient satisfaction degree and accuracy rate of acupuncture. Using the PF-X-ray, we will check the shoulder standard AP view and scapular Y view. We will rate the procedure as a success when the acupuncture needle is accurately inserted into the subacromial space.

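### The planned Neer and Hawkins comparison makes no use of the visit 2 result, although patients may enter negative on one test: valid, but some power is given away

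*Protocol article*

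**What the plan says.** Three parts of the protocol article bear on this point.

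- **Section 2.2, Inclusion and exclusion criteria.** Patients must be "with positive on the Neer or Hawkins test". One positive test is enough.
- **Section 2.5.2, Secondary outcomes.** The purpose is improvement: "To assess improvement of impingement syndrome, we will perform the Neer test and Hawkins test". On timing of the secondary outcomes: "These will be measured at visits 2, 3, and 4". Visit 2 is baseline, so each patient's starting result on each test is on record.
- **Section 2.7, Statistical analysis.** "The Neer test and Hawkins test will be summarized as frequency and percentage", and "the comparison between the 2 groups will be performed using the" chi-square or Fisher exact test. No stratification, restriction or baseline term is named. The same section does use baseline for the VAS (change from visit 2, paired t test, repeated measures analysis of variance). It extends those methods only to the modified Constant Murley score and SPADI.

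Section 2.7 does not say which visit is compared for the two tests, whether the category is positive at that visit or converted since visit 2, or which patients form the denominator.

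**The concern.** A patient who is negative on a test at visit 2 has no room to improve on it. If such patients are counted in a test's percentages, they draw the two groups together whatever the treatment does. Chance imbalance between groups in starting status adds further noise. Counting improvement over all patients does not help, because baseline negatives are then fixed non-improvers. A combined endpoint (either test positive) would avoid the problem, since everyone is positive on it at entry, but none is described.

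At stake are the power of two secondary comparisons in a small trial and how closely their estimates match the stated aim of assessing improvement.

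**Working it through.** **1. The plan's own figure.** Section 2.6 sizes the trial on the VAS: "we determined a significant difference of VAS as 2 point"; "standard deviation was conservatively assumed to be 2.3"; "We calculated the sample size with 80% power at a significance level of 0.05". Sidedness is not stated; two-sided reproduces the result:

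n per group = 2 × (1.960 + 0.842)² × 2.3² / 2² = 20.8, so 21. Dividing by 0.8 for 20% dropout gives 26.25, so 27.

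Both figures agree with section 2.6. No power is stated for Neer or Hawkins. I use 21 per group because that is the evaluable number and section 2.7 makes the per-protocol set the main one.

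**2. Assumed inputs (none is in the documents).** For one test, let q be the share positive at visit 2. Let p_C and p_E be the proportions still positive among those patients (control, experimental). Let r be the proportion of baseline negatives who are positive later, equal in both arms.

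**3. Dilution.** Over all patients the difference is

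[q·p_C + (1 − q)·r] − [q·p_E + (1 − q)·r] = q·(p_C − p_E).

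With p_C = 0.80 and p_E = 0.40, a difference of 0.40 becomes 0.36, 0.32 and 0.28 at q = 0.9, 0.8 and 0.7.

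**4. One case by hand (normal approximation, q = 0.8, r = 0).**

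- All patients: 0.64 versus 0.32, 21 per group, pooled 0.48. Null SE = √(2 × 0.48 × 0.52 / 21) = 0.154. Alternative SE = √((0.64 × 0.36 + 0.32 × 0.68) / 21) = 0.146. z = (0.32 − 1.96 × 0.1542) / 0.1461 = 0.12, so power is about 55%.
- Baseline positives only: 0.80 versus 0.40, 21 × 0.8 = 16.8 per group, pooled 0.60. Null SE = 0.169, alternative SE = 0.154. z = (0.40 − 1.96 × 0.1690) / 0.1543 = 0.45, so power is about 67%.

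**5. Simulation (200,000 trials per scenario, 21 per group, non-exact tests, two-sided 5%).**

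| p_C vs p_E | r | q | Plain chi-square | Mantel-Haenszel by visit 2 result | Baseline positives only |
|---|---|---|---|---|---|
| 0.8 vs 0.4 | 0 | 1.0 | 78% | 76% | 78% |
| 0.8 vs 0.4 | 0 | 0.9 | 65% | 73% | 74% |
| 0.8 vs 0.4 | 0 | 0.8 | 54% | 68% | 69% |
| 0.8 vs 0.4 | 0 | 0.7 | 45% | 61% | 63% |
| 0.8 vs 0.4 | 0.1 | 0.8 | 54% | 64% | 69% |
| 0.7 vs 0.4 | 0 | 0.8 | 34% | 41% | 43% |
| 0.7 vs 0.5 | 0.1 | 0.9 | 21% | 23% | – |
| 0.7 vs 0.5 | 0.1 | 0.8 | 17% | 20% | – |
| 0.8 vs 0.6 | 0.1 | 0.9 | 24% | 26% | – |
| 0.8 vs 0.6 | 0.1 | 0.8 | 18% | 22% | – |

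At 27 per group (no dropout), 0.8 versus 0.4, r = 0, q = 0.8, the three powers are 64%, 79% and 79%.

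**6. Type I error.** With 60% still positive in both arms, r = 0.1, 21 per group and q from 0.6 to 1, the plain test rejects in 4.6% to 5.0% of trials, the stratified test in 4.3% to 4.9% and the restricted test in 5.0% to 5.5%.

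**7. Reading the table.** Not all of the fall from 78% is due to the choice of test. At q = 0.8, baseline-positive analysis still reaches only 69%, because fewer patients carry information. The part that a better analysis recovers is the gap between the plain column and the other two.

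**The case against.** The strongest case against is that section 2.7 fixes very little. It names no visit, category or denominator, and a chi-square on conversion among visit 2 positives would fit its wording. An analysis plan that is not shown may settle this. The planned test holds its type I error, the outcome is secondary, and the trial promises no power for it. The primary VAS is itself scored during the Neer and Hawkins manoeuvres (section 2.5.1) and analysed as change from visit 2, so improvement on them is already captured on a continuous scale. Finally, a 40-point difference is large for two active arms needling the same points.

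Much of this stands. A reader might infer that the plan definitely compares prevalence at follow-up over all patients; the text does not say so. A reader might also infer bias or an invalid test; randomisation and the null simulation rule that out. A general claim that the loss is large is unsupported too, because it depends on an effect size and a baseline share that the documents do not give.

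What does not fall is the core. The article does not leave the method open: it names a test with no baseline term for these two outcomes, while giving baseline handling to the VAS, modified Constant Murley score and SPADI. Using a result already collected improves on that stated method.

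**Conclusion.** The point holds as a modest loss of efficiency and a loose fit to the stated purpose, on a secondary outcome. In every simulated scenario with some baseline negatives and a true effect, using the visit 2 result gave more power, with type I error near 5%.

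The size rests wholly on assumptions. With 21 evaluable per group, 80% versus 40% still positive among baseline positives, and baseline negatives staying negative, stratifying adds about 8 points of power at 90% positive at baseline and about 16 at 70%. For 20-point effects with 10% of baseline negatives turning positive, and 70% to 90% positive at baseline, it adds only about 2 to 5 points, and either analysis is badly underpowered. If all patients are positive on both tests there is nothing to recover. The primary VAS analysis and the sample size are unaffected. Priority is low.

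**What to change.** In section 2.7, for each of the two tests:

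- Make the between-group comparison a Mantel-Haenszel test stratified by that test's visit 2 result.
- As a supporting analysis, report conversion to negative among patients positive on that test at visit 2. This subset is defined before treatment, so the randomised comparison is kept.
- State the visit and the category compared.
- Keep the raw frequencies and percentages as description.

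If cells are small, use an exact version and expect somewhat less power than shown above. For example, at 27 per group with 70% positive at baseline and 80% versus 40%, Fisher's test among baseline positives gives about 66%, against about 73% for the chi-square.

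The cost is a few sentences of analysis wording. No new data, visits or patients are needed.

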### Study design and ethics approval

2.1

This study will be a randomized, patient-assessor blind, controlled clinical trial with 2 parallel groups. The protocol of this study has been approved by the institutional review board (IRB) of Wonkwang University Gwangju Hospital (WKIRB-2017/13) on October 28, 2017. This trial study will be conducted in Wonkwang University Gwangju Hospital in Korea according to the ethical principles of the “Helsinki Declaration.” We will make a poster and advertise it to recruit participants. Before screening for participating in this trial, participants will receive information about the trial. Researchers will proceed with the trial after obtaining a voluntary signature consent, and any identifiable records will be kept confidential. Recruited participants will be randomly assigned to 2 groups: acupuncture treatment with fluoroscopy-guided implementation and acupuncture treatment with proportional measurements. There is a 1-week run-in period before randomization, and total study periods will be 3 weeks, including a 2-week follow-up period. Participants will receive 2 sessions of acupuncture treatment: at baseline (visit 2) and 1 week later (visit 3) (Fig. 1).

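### LOCF enters a patient with no visit 3 VAS as exactly zero change in the visit 3 comparison, which distorts the FAS result and, if such patients are kept, the PPS result

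*Protocol article*

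**What the plan says.** Section 2.7 (Statistical analysis) names one method for missing data: "In the case of missing data, the method of last observation carried forward (LOCF) will be performed". It is not limited to a variable or an analysis set.

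The same section fixes the primary comparison: "Evaluation of the primary outcome will be conducted by VAS change after 2 treatment sessions (visit 3) compared with baseline (visit 2"). The test is stated as follows: "To compare 2 groups, 2-sample *t* test will be used". For the time course it adds: "For the interaction of treatment over time, repeated measures analysis of variance will be used". Efficacy is analysed in both the FAS and the PPS, and "PPS will be the main set according to the principle of intentionality treatment".

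Section 2.5.1 (Primary outcome) gives the VAS schedule: "This outcome will be measured at visits 2, 3, and 4". Section 2.1 (Study design and ethics approval) gives the treatment schedule: "Participants will receive 2 sessions of acupuncture treatment: at baseline (visit 2) and 1 week later (visit 3"). Section 2.6 (Sample size) allows for losses: "Assuming a dropout of about 20"%.

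**The concern.** Visit 2 is the baseline and the only scheduled VAS value before visit 3. For the comparison as written, LOCF therefore reduces to carrying the baseline forward: whoever misses visit 3 is recorded as not having changed at all. Both arms receive real acupuncture, so improvement in both is plausible and zero is unlikely to be the typical unobserved change.

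Three things are at stake.

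- If losses are equal, the zeros pull the difference between groups towards zero and add spread.
- If losses are unequal, the arm with more of them looks worse even when the treatments do not differ.
- The t test and the repeated measures ANOVA both treat the filled values as data, so the standard errors do not reflect that they are missing.

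The sample size adds to the problem. The step from 21 to 27 per group replaces patients who leave the analysis; under LOCF they stay in it as zeros.

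**Working it through.** **Inputs from the article.** Difference 2 points, SD 2.3, significance level 0.05, power 80%, 21 per group, about 20% dropout, 27 per group (all section 2.6); allocation 1:1 (section 2.3).

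**Assumptions.** Points are read as 0-10, so 2 points is 20 mm and 2.3 is 23 mm. The test is two-sided. The SD is applied to the change score. The article gives neither the control improvement nor the share of patients missing at visit 3, so ranges are used: 10, 20 and 30 mm, and 5%, 10% and 20%. Patients are missing at random with respect to their change.

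**Step 1: the plan's own figure.** n per group = 2 × 2.3² × (1.96 + 0.84)² / 2² = 20.7, rounded up to 21. Inflated: 21 / (1 − 0.20) = 26.25, rounded up to 27. Both stated figures reproduce.

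**Step 2: zero-filling with equal losses.** Let a fraction d of each arm be set to zero, and let μ be the arm's true mean change.

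- Expected difference = (1 − d) × 20 mm.
- Arm variance = (1 − d) × 23² + d(1 − d) × μ².

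Example with d = 0.20 and a control improvement of 20 mm (experimental 40 mm):

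- Difference: 0.8 × 20 = 16 mm.
- Control variance: 0.8 × 529 + 0.16 × 400 = 487.2.
- Experimental variance: 0.8 × 529 + 0.16 × 1600 = 679.2.
- Pooled SD: √583.2 = 24.15 mm.
- Power of the t test with 27 per arm: 67%.

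Simulated power over the range (two-sample t test, 27 per arm):

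| Missing at visit 3, each arm | Expected estimate | Power, control improvement 10 / 20 / 30 mm |
|---|---|---|
| 5% | 19 mm | 85 / 83 / 80-81% |
| 10% | 18 mm | 81 / 78 / 73% |
| 20% | 16 mm | 73 / 66-67 / 59% |

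**Step 3: the comparator.** Omitting the missing patients leaves the 20 mm difference undiluted under the same assumption. At 20% missing, 27 × 0.8 = 21.6 patients per arm give about 80% power; at 10%, 24.3 give about 84%; at 5%, 25.65 give about 86%. The 88% that 27 complete patients per arm would give is not the right reference, because the plan does not expect to have them.

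**Step 4: no true difference, unequal losses.** Both arms improve by μ, so the false difference is μ × (the difference in missing fractions), against the arm with more losses.

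| Missing | μ = 10 mm | μ = 20 mm | μ = 30 mm |
|---|---|---|---|
| 10% vs 30% | 2 mm, type I error 6.5% | 4 mm, about 10.6% | 6 mm, 15.5% |
| 15% vs 25% | 1 mm, about 5% | 2 mm, about 6% | 3 mm, about 7.5% |
| 20% vs 20% | 0 mm, about 5% | 0 mm, about 5% | 0 mm, about 5% |

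**Step 5: unequal losses with a true 20 mm difference.** With 30% missing in the experimental arm and 10% in control, the estimate is 0.7 × (μ + 20) − 0.9 × μ, which is 12, 10 or 8 mm for a control improvement μ of 10, 20 or 30 mm. With the losses reversed it is 0.9 × (μ + 20) − 0.7 × μ, which is 20, 22 or 24 mm. The error is not always a dilution.

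**The case against.** **The main set is the PPS.** A patient who misses visit 3 also misses the second session, which section 2.1 places there, and may well be excluded from a per-protocol set. This stands. A reader might infer that LOCF biases the trial's main result; the article does not support that, because it does not say whether the PPS keeps such patients. The figures above apply to the FAS, or to a PPS that retains them.

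**The 20% is an overall allowance.** Patients lost after visit 3 have an observed visit 3 value and need no filling there. This also stands: the 20% row places every loss in the single week between visits 2 and 3, so 59-73% is the low end of the range and not a forecast.

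**Nothing in the article points to unequal losses.** Both arms are needled at the same points, and patients and assessors are blinded. A reader might take the 15.5% type I error as the trial's error rate. It requires both a 10% vs 30% split and a 30 mm improvement in both arms, and neither is in the article.

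**The primary visit is itself unclear.** Section 2.7 describes visit 3 as following two sessions, while section 2.1 gives the second session at visit 3. If visit 4 was meant, zero change applies only to patients lost before visit 3, and later losses carry their visit 3 value. That narrows the problem without removing it.

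**A mixed model cannot recover visit 3 for patients lost before it.** This is correct and limits what the fix can claim. The rule is nevertheless stated in the article, so the point does not rest on detail left to an unseen analysis plan.

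**Conclusion.** The concern holds with a limited scope. For the visit 3 comparison as written, LOCF assigns exactly zero change to anyone without visit 3 and treats it as observed. That is certain from the VAS schedule; its size is not.

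In the FAS, with 5% to 20% missing equally in each arm, a true 20 mm difference shrinks to 19 to 16 mm. At 20% missing, power is 59-73% where leaving those patients out would give about 80%; at 5% missing the loss is small. Bias in either direction and an inflated type I error need unequal losses; equal losses leave the error rate at about 5%. All of this depends on the assumed improvement, the timing and balance of losses, and the reading of SD 2.3 as the SD of change. The effect on the main PPS analysis cannot be determined from the article.

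**What to change.** In section 2.7, replace LOCF as the main method with a likelihood-based mixed model for repeated measures on the visit 3 and visit 4 VAS, without imputation. Its terms are group, visit, group by visit, and baseline VAS. Take the primary contrast at the primary visit once sections 2.1 and 2.7 have been reconciled. Keep LOCF only as a secondary sensitivity analysis.

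Add a delta-adjusted sensitivity analysis, in which unobserved outcomes are assumed worse than predicted by a stated range of shifts, including different shifts by arm. LOCF alone cannot test the model's assumption.

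State whether a patient without visit 3 stays in the PPS.

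The cost is a few sentences in section 2.7 and standard SAS code, with no new visits, data or patients. The downside is that the model assumes missing at random. Patients lost before visit 3 contribute no outcome after baseline, so for them it is close to a baseline-adjusted complete-case analysis. It gains information at visit 3 only from patients who miss that visit but attend visit 4.
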